## Statistical methods

An online, quality-assured, digital database will be created containing the data. The analyses will be performed with SPSS statistical package (version 17.0; SPSS, Chicago, Illinois). Patient’s demographics, gender, age, height, weight, affected side will be described for both treatment groups and safety will be assessed by identifying and summarizing complications and other clinically relevant adverse events collected throughout the study. Continuous data will be presented as the mean (and standard deviation) if normally distributed (according to Fischers exact or eyeball test); otherwise, the medians (with range) will be reported. Dichotomous data will be presented as frequencies (with accompanying percentages).

To check the distribution of the baseline characteristics, the treatment groups will be compared using Student’s t-tests or chi-square tests, depending of the type of outcome measure.

The primary endpoint – number of weeks until patients achieved radiological union postoperatively – will be analyzed using a student’s *t*-test or equivalent; this parameter will be used for clinical union as well. A chi-square test will be used to analyze union rate at each time point, and a student’s *t*-test will be used to determine statistical differences in time to return to work and/or sport. Patient-reported outcome measures will be analyzed using a student’s *t*-test or repeated measures ANOVA.

Risk factors for the development of healing problems (such as smoking behavior, BMI, and age) will first be identified using univariate analysis (t-tests, chi-squared tests). In case of significance (significance level will be set at 0.1), the risk factors will be entered in a multivariate logistic regression model. The cBMA analysis will be reported as absolute cell count and in % of cell types. Data on the bone biopsies of the stress fractures will be descriptive.

A comprehensive, updated sample size justification and statistical plan will be created together with an interim report after the interim analysis.

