## Background

Marines, soldiers and athletes are prone to fractures due to extensive and repeated stress on (usually weight bearing) bones [1–4]. These stress fractures develop over time and are therefore different than the more commonly accounted traumatic fractures. The damage caused by repeated forces on the bone outruns the natural remodeling process in loaded bones, resulting in a weak spot or ‘stress reaction’ and eventually a stress fracture [5–7]. Due to the increasing sports participation in the general population and awareness of their existence, these types of fractures are more frequently diagnosed. Of all stress fractures of the lower leg, the stress fracture of the fifth metatarsal has one of the highest incidences, namely up to 25 % [8]. This issue is amplified in the patients that depend on perfect physical condition like professional athletes. In a recent review of the literature, it is described that operative treatment of fifth metatarsal stress fractures results in smaller number of delayed unions or non-unions, compared to conservative treatment [9]. Still, the time to return to activity varies from 12 to 18 weeks [9–12].

Compared to a normal, traumatic fracture, stress fractures do not seem to heal via callus formation, but rather by primary bone healing with remodeling across the fracture line [7, 13, 14]. This process is slower with a higher propensity to fail, resulting in a complete fracture and refractory healing, similar to non-union [7, 14]. In traumatic fractures healing starts with formation of hematoma and therewith release of inflammatory cells. The next phase is recruitment of mesenchymal cells that differentiate into osteoblasts resulting in primary bone formation with callus production followed by secondary bone formation, with bone remodeling. In stress fractures, healing starts with the remodeling phase. Via early woven bone formation, callus is only formed along the exit point of the fracture towards the medullary cavity [15, 16].

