### Outcome measures

The primary endpoint is the time to radiographic union in weeks.

The secondary endpoints are: time to clinical union, time to return to work and/or sport (in weeks), union rate at each time point (in %), patient function and satisfaction (SF-36, FAOS, FAAM), complication rate and cost-effectiveness (SF-HLQ), compared between intervention and control group.

During the operation a bone biopsy is taken. This will be histologically analyzed. From the obtained cBMA a 2 ml sample will be analyzed (flow cytometry and a multiplex assay for detecting CD 31, CD 34, CD 45, CD 90, CD 105, CD 166 amounts, CFU-F assay and mRNA analysis).

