### Secondary outcomes

Clinical union will be measured during physical examination. Pain on axial compression force and pain on the fracture site during palpation will be monitored through a patient-based VAS score. When patients still report significant pain, measured as a VAS > 3 on a Visual Analogue Scale from 0 to 10 [31, 32], clinical union is not yet achieved. Return to sports is defined as the time (in weeks) to resumption of weight-bearing sports after surgery and the level should be maintained for at least 30 days [33]; return to work is defined in the same way. When returned to sport, but activity level decreases to below the start level within 30 days after resumption, then this will be deemed as a failed return to activity and the date will not be counted. From the 6^th^ till the 14^th^ week, most unions are expected to occur. On each of these biweekly time points a union rate will be counted; number of unions at t = XXX divided by total sample size (%).

The SF-36 is a patient-administered, generic health related quality of life instrument [34, 35]. The FAOS was developed to assess the patients’ opinion about a variety of foot and ankle-related problems [36]. The results can be presented as an outcome profile. The FAAM is a 29-item questionnaire. The FAAM consists of 2 subscales: Activities of Daily Living and Sports [37].

Cost-effectiveness is analyzed using the The EuroQol (EQ-5D) [38, 39] and the SF-36, FAOS, FAAM as measurement for effectiveness of treatment. Costs are calculated from the SF HLQ [40, 41] and the cost of the investigated intervention. The questionnaire consists of 11 questions and provides information about labor (missing) costs and additional paid working hours.

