### Data acquisition and follow-up

Participating patients will be assessed at the following time points (Table 1):

**Table 1 Tab1:** Schedule for screening and follow-up of included participants

Screening and Follow-Up Clinical and Radiographic Exams						
Action	Pre-operative	Intra-operative	Follow-Up Visit (biweekly 2-14 weeks)	Follow-Up Visit Until Union (biweekly) (>14 weeks, determined by physician)	6 month follow-up visit	1 year Follow-Up visit
Information letter	X					
Obtain written informed consent	X					
Complete eligibility checklist	X					
Complete medical history and baseline characteristics (form)	X					
Complete physical examination (form)	X		X	X	X	X
Surgery		X				
- Operative form (surgical information)		X				
- cB + cBMA preparation and administration		X				
- Bone biopsy fracture site		X				
Lab assessments	X					
Questionnaires	X		X		X	X
Radiographic assessment	X	X	X	X	X	X
Complication (form)	X	X	X	X	X	X
Adverse events, withdrawals & re-operation (form)	X	X	X	X	X	X

before inclusion: information letter, complete reliability checklistpreoperatively (after an enrollment period of two weeks): informed consent, complete reliability checklist, baseline characteristics (age, gender, weight, height, affected side, duration of symptoms, smoking status, AAS before symptoms and at preoperative assessment, past medical history, medication used), type of sport and profession, local physical examination with VAS, laboratory assessment (Hemoglobin levels, leucocytes, sodium, potassium, urea and creatinine), FAOS, FAAM, SF-36, EQ-5D, SF HLQ, X-ray (AP oblique and lateral);intraoperative: cB + cBMA preparation and administration, bone biopsy of the fracture site, right after internal fixation an X ray (AP, oblique and lateral) and an operative form (surgical information) with complications and (S)AEs if applicable;biweekly 2-14 weeks postoperatively: wound inspection, local physical examination with VAS, FAOS, FAAM, SF-36, EQ-5D, TiC, X-ray (best view for analyzing the fracture), resumption of sports and work, complications and (S)AEs;six months postoperatively: local physical examination with VAS, FAOS, FAAM, SF-36, EQ-5D, TiC, X-ray (best view for analyzing the fracture), resumption of sports and work, complications and (S)AEs;one year postoperatively: local physical examination with VAS, FAOS, FAAM, SF-36. EQ-5D, TiC, X-ray (best view for analyzing the fracture), resumption of sports and work, complications and (S)AEs

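### Return to work and sport is fixed to an unadjusted t-test although profession and pre-symptom activity are recorded at baseline: valid, but it may lose precision, mainly for return to work

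*Protocol article*

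**What the plan says.** The Outcome measures section lists time to return to work and/or sport, in weeks, as a secondary endpoint. The Statistical methods section assigns it a Student's t-test, which "will be used to determine statistical differences in time to return to work and/or sport". For the primary endpoint the same paragraph leaves room for an equivalent test; for this endpoint it does not. No covariate is named. The section's only regression is a logistic model for healing problems, with smoking, BMI and age as examples.

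The Data acquisition and follow-up section lists, among the preoperative items, "type of sport and profession" and the "AAS before symptoms and at preoperative assessment". (The article does not spell out AAS; it is read here as an activity score.) Neither item has a role in the return-to-work or return-to-sport comparison. The Randomization section describes permuted blocks of 4, 6 or 8 and names no stratification factor.

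Under Secondary outcomes, a return to sport does not count if the patient's "activity level decreases to below the start level within 30 days after resumption". For work, the text says only that "return to work is defined in the same way", with no reference to the type of work.

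**The concern.** Return to work may depend on what the job asks of the foot as well as on healing. Both arms spend the first 8 weeks in a cast or walker. It is a reasonable inference, though not a statement in the article, that some seated work can resume in that time while physically loading work cannot. The eligibility criteria do not restrict occupation, so a mix of jobs is possible. If job types differ in their typical return time, that difference enters the error term of an unadjusted t-test and widens the confidence interval for the treatment effect. The variable that would remove it is already on the baseline form.

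For sport the argument is weaker. That endpoint concerns weight-bearing sport and is judged against the patient's own starting level, so it is already partly patient-specific. A quicker return to sports or activities is, however, a stated hypothesis under Objectives and hypothesis, so precision there also has some value.

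A smaller point is that the and/or in the analysis sentence does not say whether one or two comparisons are meant, although the definitions treat work and sport separately.

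**Working it through.** **1. The plan's own figure.** The Sample size section concerns radiological union only: means of 12 and 10 weeks, SD 1.88, 90 % power, 20 per arm, 25 after 20 % dropout. Effect size is 2/1.88 = 1.06. Two-sided noncentral t power at 0.05 is 0.891 with 19 per arm and 0.906 with 20; 20/0.8 = 25. The figure reproduces. It says nothing about return to work or sport.

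**2. What the article gives for return to work or sport.** There is no SD, no effect size and no split by job. The Background cites a time to return to activity of 12 to 18 weeks, without an SD. Everything below is therefore an illustration under assumptions.

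**3. Assumptions.** Two job classes, half the patients in each; SD within class 3 weeks; true effect 2 weeks (borrowed from the primary endpoint); 20 per arm; two-sided 0.05. The mean gap g between job classes is varied.

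- Unadjusted SD = √(3² + 0.25·g²)
- Share of variance due to job = 0.25·g² / (9 + 0.25·g²)
- Noncentrality = 2 / (SD·√(2/20)), with 38 degrees of freedom

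| Gap g (weeks) | Unadjusted SD | Job share of variance | Power, unadjusted |
|---|---|---|---|
| 2 | √10 = 3.16 | 10 % | 0.50 |
| 4 | √13 = 3.61 | 31 % | 0.40 |
| 6 | √18 = 4.24 | 50 % | 0.31 |
| 8 | √25 = 5.00 | 64 % | 0.23 |
| 10 | √34 = 5.83 | 74 % | 0.19 |

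Adjusted for job class, the residual SD is 3 and power is 0.54 in every row. Charging one degree of freedom (37 instead of 38) does not change this to two decimals.

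**4. A different residual SD.** If the within-job SD were 1.88 weeks, as assumed for union, unadjusted power would be 0.88, 0.81, 0.64 and 0.37 when the baseline variables explain 10, 25, 50 and 75 % of the variance, against about 0.91 adjusted. The pattern is the same: a small loss at a low share and a large one at 50 % or more.

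**5. Validity.** A simulation of 20,000 trials with no treatment effect, two job types 6 weeks apart, within-job SD 1.88 and 20 per arm gave the unadjusted t-test a type I error of 0.050 and a mean bias of about 0.0 weeks.

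**6. Chance imbalance.** With g = 6 and 20 per arm, the variance of the unadjusted difference is 2·18/20 = 1.80. Of this, 2·9/20 = 0.90 comes from unequal job mix, an SD of 0.95 weeks. That part is already inside the SD of 4.24 used in step 3. It is not an additional harm.

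**The case against.** The strongest case against is that an unadjusted comparison is legitimate in a randomised trial, that covariates for a secondary endpoint are commonly left to the analysis plan, and that the Statistical methods section foresees an updated statistical plan after the interim analysis. On this view the point is a preference. Part of that stands: the article says nothing false here, and the endpoint is secondary and was never powered. What does not stand is that the matter is simply left open, because the article names a specific test for this endpoint.

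A reader might infer that job differences swamp the treatment effect or make up most of the variance. The documents do not support that. They give no return-to-work SD and no job split, and in the illustration job is the majority of the variance only at gaps of 8 and 10 weeks. A reader might also infer that chance imbalance in jobs makes the result untrustworthy. Step 6 shows that the t-test's standard error already carries it, and step 5 shows no inflation of error. Finally, the Background remark that "Marines, soldiers and athletes are prone to fractures due to extensive and repeated stress" describes who tends to get these fractures. It does not describe whom this trial recruits, so the actual job mix is unknown.

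The gain from adjustment is also limited. At 54 % the adjusted analysis remains underpowered in the illustration, and that figure keeps 20 per arm although patients without paid work would not contribute. Adjusting for type of sport, with its many categories, could cost precision at about 20 per arm.

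**Conclusion.** The point holds as one of efficiency. The plan fixes an unadjusted t-test for time to return to work and/or sport and leaves recorded, plausibly prognostic baseline data unused. The test is valid. The possible loss of precision falls mainly on return to work, and the documents do not allow it to be quantified. With a within-job SD of 3 weeks, an even job split, a 2-week effect and 20 per arm, the power given up runs from about 4 percentage points (54 against 50 %) at a 2-week job gap to about 35 (54 against 19 %) at 10 weeks. The article does not say where in that range the trial lies. The endpoints are secondary and the primary analysis is unaffected, so this is a minor improvement.

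**What to change.** State return to work and return to sport as two separate secondary endpoints, in line with their separate definitions.

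- **Return to work:** among patients in paid work before surgery, compare arms with adjustment for the physical demand of the profession in two classes. Code the classes from the baseline form, blind to allocation.
- **Return to sport:** adjust for the pre-symptom AAS as a single covariate. Do not adjust for type of sport.

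The updated statistical plan that the article already foresees is a natural place for this, provided that the choice is made without sight of results by arm. No new data are needed. The cost is one blinded coding of 50 baseline forms, one degree of freedom per model, and fewer patients in the return-to-work analysis, since those without paid work before surgery leave it.

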## Withdrawal of subjects

Subjects can leave the study at any time for any reason if they wish to do so, without any consequences. The investigator can decide to withdraw a subject from the study for urgent medical reasons. Subjects will not be replaced after withdrawal. Data of a withdrawn subject will be used, but we will delineate from which visit (time point) data is incomplete and (if known) why the subject is sequestered. To investigate why subjects are withdrawn, they will be contacted by telephone and/or letter to assure the reason for their withdrawal and to ask them to come in for an optional final visit.

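### The patient-reported outcomes have a preoperative score and nine postoperative visits, but the two named analyses use the baseline poorly or not at all, and one of them needs complete cases

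*Protocol article*

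**What the plan says.** Statistical methods gives one sentence on these outcomes: "Patient-reported outcome measures will be analyzed using a student’s *t*-test or repeated measures ANOVA". It does not say which of the two tests applies when, whether the t-test is on raw or change scores, or which visit is of main interest. It names no baseline covariate.

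The instruments are secondary endpoints under Outcome measures: "patient function and satisfaction (SF-36, FAOS, FAAM), complication rate and cost-effectiveness (SF-HLQ), compared between intervention and control group".

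Data acquisition and follow-up sets the schedule:

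- Before surgery, the list includes "FAOS, FAAM, SF-36, EQ-5D, SF HLQ, X-ray (AP oblique and lateral".
- Early follow-up: "biweekly 2-14 weeks postoperatively: wound inspection, local physical examination with VAS, FAOS, FAAM, SF-36, EQ-5D, TiC".
- Then "six months postoperatively: local physical examination with VAS, FAOS, FAAM, SF-36, EQ-5D, TiC", and finally "one year postoperatively: local physical examination with VAS, FAOS, FAAM, SF-36. EQ-5D, TiC".

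FAOS, FAAM and SF-36 (and EQ-5D) therefore have one preoperative score and nine postoperative ones. The SF HLQ is listed only before surgery and the TiC only afterwards, so neither is part of this point.

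On patients who leave, Withdrawal of subjects says: "Data of a withdrawn subject will be used, but we will delineate from which visit (time point) data is incomplete".

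**The concern.** With at most 25 patients per arm, the functional scores can show only large differences. A preoperative score on the same instrument is the most obvious covariate for recovering precision, and here it is already being collected. The named methods either leave it out or use it less efficiently than a covariate adjustment would.

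The ANOVA option raises a second issue. In its classical form a patient enters only with a score at every occasion analysed. With up to ten occasions and an allowance for dropout, a patient who withdraws late would contribute nothing, although the protocol intends that patient's data to be used. If patients who heal poorly leave more often, the remaining complete cases are also a selected group.

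**Working it through.** **The plan's own figure.** The only sample-size figure is for the primary outcome (Sample size section): means of 12 and 10 weeks, SD 1.88, 90% power, significance level 0.05 (taken as two-sided). The effect size is 2/1.88 = 1.06. The noncentral t distribution gives power of 89.1% with 19 per arm and 90.6% with 20, so 20 per arm reproduces. With 20% dropout, 20/0.8 = 25 per arm, or 50 in total. No figure is given for the patient-reported outcomes.

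**Number of occasions.** Weeks 2, 4, 6, 8, 10, 12 and 14 make 7 visits. Adding 6 months and 1 year gives 9 postoperative visits, or 10 occasions with baseline.

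**Precision.** Let r be the correlation between the preoperative score and the score at one follow-up visit, with equal SDs. Take the variance of the arm difference from a t-test on follow-up scores as 1.

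- Baseline-adjusted (ANCOVA): 1 − r².
- Change from baseline, which is also what the group-by-time contrast of an ANOVA with baseline as a time level amounts to: 2(1 − r).
- The ratio of change score to ANCOVA is 2(1 − r)/(1 − r²) = 2/(1 + r), which exceeds 1 for every r below 1.

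The protocol gives no r, so a range is assumed. Detectable differences are at 80% power, two-sided 0.05, in SD units of the score. The ANCOVA columns include a finite-sample penalty of 1 + 1/(2n − 4), with n per arm.

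| r (assumed) | ANCOVA variance | Change-score variance | Cut vs. t-test | Detectable, 25/arm, ANCOVA | Detectable, 20/arm, ANCOVA |
|---|---|---|---|---|---|
| 0.2 | 0.96 | 1.60 | 4% | 0.80 | 0.90 |
| 0.3 | 0.91 | 1.40 | 9% | 0.78 | 0.88 |
| 0.5 | 0.75 | 1.00 | 25% | 0.71 | 0.80 |
| 0.7 | 0.51 | 0.60 | 49% | 0.58 | 0.66 |

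For the unadjusted t-test the detectable difference is 0.81 SD with 25 per arm and 0.91 SD with 20.

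The change score is worse than ignoring baseline when 2(1 − r) > 1, that is when r is below 0.5. With 25 per arm the penalty is 1 + 1/46 = 1.022. At r = 0.2 the net ANCOVA variance is then 0.98, so the gain is close to nil at that end of the range.

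**Complete cases under classical repeated measures ANOVA.** Dropout at the planned maximum leaves 50 × 0.8 = 40 patients. If a share p of the remaining patients' visits is missed, independently (an assumption), the number complete over the nine postoperative visits is 40 × (1 − p)^9:

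- p = 1%: 36.5
- p = 2%: 33.3
- p = 5%: 25.2
- p = 10%: 15.5

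Only the figure of 40 rests on the protocol's own numbers. The others depend on p, which the protocol does not give, and on dropout reaching its stated ceiling.

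**The case against.** The strongest reply is that these are secondary outcomes, that the article does not prescribe deletion of incomplete patients, and that missing-data detail belongs in an analysis plan which may exist. Part of this stands. Deletion is a consequence of one of the two named methods, not something the protocol states, and a t-test at one visit loses only the patients not seen at that visit. However, the choice of methods is itself written into the protocol, so it can be judged as written.

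It can also be said that a repeated measures ANOVA with baseline as a time level does use baseline. That is correct, and it would be wrong to say that both methods ignore it. The loss under that option comes from using baseline as a change score.

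The gain may also be small. Patients are in a cast or walker for the first 8 weeks (Standard treatment and investigational treatment), so correlation with preoperative function could be low at the early visits. This is why the range above starts at 0.2.

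Two stronger readings are tempting and are not supported:

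- A reader might count 3 instruments × 9 visits = 27 t-tests and infer a high risk of a false-positive result. The protocol mentions testing at each time point only for union rate, not for these scores. Any rate computed as if the 27 tests were independent would also be too high, because the scores come repeatedly from the same patients.
- A reader might infer that chance imbalance at baseline biases the unadjusted comparison. Under randomisation it does not, since the standard error already allows for it. The cost is precision, not validity.

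**Conclusion.** The point holds as an avoidable inefficiency in the secondary outcomes. Compared with an unadjusted t-test on follow-up scores, baseline adjustment cuts the variance by 4% to 49% for an assumed r of 0.2 to 0.7. It is more efficient than a change-score analysis at every r below 1, apart from the small finite-sample penalty. The true gain cannot be fixed from the protocol, because r is not given.

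If the classical ANOVA is the option used, complete-case analysis could reduce 50 patients to 40 from the planned maximum dropout alone, and to fewer with sporadic missed visits. That is in tension with the statement "Data of a withdrawn subject will be used". It is not a direct contradiction, because the protocol does not say that incomplete patients will be dropped.

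The primary endpoint, its analysis and the sample size are untouched.

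**What to change.** Replace the sentence on patient-reported outcomes, including its choice between two tests, with one linear mixed model per score:

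- Fixed effects: preoperative score, arm, visit and arm-by-visit.
- Data: all available postoperative visits, so a withdrawn patient contributes every score obtained up to withdrawal.
- Covariance: a prespecified structure that 50 patients can support. An unstructured matrix over nine visits has 9 × 10/2 = 45 parameters, which is too many here.
- Reporting: the arm difference at one prespecified visit with its 95% CI, and the other visits descriptively.

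The model does not protect against dropout that depends on unobserved outcomes, so reasons for withdrawal should still be recorded as planned.

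The cost is a change of wording, with no new data or visits. It should be made before the interim analysis. Statistical methods promises an updated statistical plan only after that analysis, when outcome data will have been seen, whereas the publication policy section describes the trial as not yet recruiting.
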